## **List of Abbreviations**

|     |                            |
|-----|----------------------------|
| AE  | Adverse Event              |
| CRF | Case Report Form           |
| SAE | Serious Adverse Event      |
| BRS | Baroreflex Sensitivity     |
| SNS | Sympathetic Nervous System |
| HRV | Heart Rate Variability     |
| RHR | Resting Heart Rate         |
| BPV | Blood Pressure Variability |
| EH  | Essential Hypertension     |
| PP  | Per Protocol               |
| ITT | Intention to Treat         |

## 1. Synopsis

|                                     |                                                                                                                                                                                                                                                                                                                                                                                                                                                                                                                                                                                                                                                                                      |
|-------------------------------------|--------------------------------------------------------------------------------------------------------------------------------------------------------------------------------------------------------------------------------------------------------------------------------------------------------------------------------------------------------------------------------------------------------------------------------------------------------------------------------------------------------------------------------------------------------------------------------------------------------------------------------------------------------------------------------------|
| Study title                  | Effects of bisoprolol and atenolol on resting heart rate, sympathetic nervous system's activity and central blood pressure in patients with essential hypertension (Biso-ARTS Study)                                                                                                                                                                                                                                                                                                                                                                                                                                                                                                 |
| Study center(s)/country(ies) | 1 site/China                                                                                                                                                                                                                                                                                                                                                                                                                                                                                                                                                                                                                                                                         |
| Study Phase                  | Phase IV                                                                                                                                                                                                                                                                                                                                                                                                                                                                                                                                                                                                                                                                             |
| Planned study period         | First Patient In: September.2010
Database Lock: October.2011                                                                                                                                                                                                                                                                                                                                                                                                                                                                                                                                                                                                                      |
| Study objectives             | 
Primary objective
 
To compare the efficacy in SNS activity and central blood pressure(CAP) of bisoprolol and atenolol in essential hypertensive patients with RHR>70bpm
 
Secondary objective
 
 
1. To compare the effect in other SNS indication of bisoprolol and atenolol in EH patients with RHR>70bpm
 
2. To compare the efficiency of bisoprolol and atenolol to attaining RHR<65bpm]
 
3. To compare the efficiency of bisoprolol and atenolol on peripheral blood pressure
 
4. To compare the safety and compliance of bisoprolol and atenolol treatment after RHR<65bpm
 
 |
| Study design and plan        | 
A phase IV single-centre randomize controlled study. The patient will receive bisoprolol 5mg Qd.(or atenolol 25mg Bid) for 2 weeks. If his/her heart rate<65bpm, this initial dose will be prolonged for another 2 weeks before the observation is over.
 
If the heart rate>65bpm, the patient will receive bisoprolol 7.5mg Qd.( or atenolol 37.5mg Bid) for 2 weeks. Then if his/her heart rate<65bpm, this
                                                                                                                                                                                                                                                  |

|                                                            |                                                                                                                                                                                                                                                                                                                                                                                                                                                                                                                                                                                                                                                                                                                                                                                                                                                                                                                                                                                                                                                                                                                                                      |
|------------------------------------------------------------|------------------------------------------------------------------------------------------------------------------------------------------------------------------------------------------------------------------------------------------------------------------------------------------------------------------------------------------------------------------------------------------------------------------------------------------------------------------------------------------------------------------------------------------------------------------------------------------------------------------------------------------------------------------------------------------------------------------------------------------------------------------------------------------------------------------------------------------------------------------------------------------------------------------------------------------------------------------------------------------------------------------------------------------------------------------------------------------------------------------------------------------------------|
|                                                            | 
increased dose will be prolonged for another 2 weeks before the observation is over.
 
If the heart rate>65bpm, the patient will receive bisoprolol 10mg Qd.( or atenolol 50mg Bid) for 2 weeks. Then if his/her heart rate<65bpm, this increased dose will be prolonged for another 2 weeks before the observation is over. If the heart rate>65bpm, the observation is over directly.
                                                                                                                                                                                                                                                                                                                                                                                                                                                                                                                                                                                                                                                                                                                                         |
| Planned number of subjects                          | 110patients                                                                                                                                                                                                                                                                                                                                                                                                                                                                                                                                                                                                                                                                                                                                                                                                                                                                                                                                                                                                                                                                                                                                          |
| Diagnosis and main inclusion and exclusion criteria | 
Main Inclusion Criteria including:
 
 
1. 25~65 years old
 
2. Untreated mild to mederate EH
 
3. Sinus rhythm
 
4. RHR >70bpm
 
5. Can give written informed consent
 
 
Main Exclusion including including:
 
 
1. Atrial Fibrillation (AF)/ Sick Sinus Syndrome (SSS)/ atrioventricular block 2-3 grade(AVB II III) without pacemaker
 
2. Bradyrrhythmia
 
3. hypotensive
 
4. Unstable Angina Pectoris (UAP)/AMI/ HF (NYHA class III - IV)
 
5. Uncontrolled diabetes mellitus (DM)
 
6. Bronchial asthma
 
7. Gastro-intestinal ulcer or skin ulcer
 
8. Liver dysfunction/ renal impairment
 
9. Treated with CCB (Calcium antagonists) ( except amlodipine) or other beta blocker.
 
10. Glaucoma
 
11. Known allergic/ intolerance to beta blocker
 
12. Pregnant or lactating women
 
13. Participation in another clinical study within th last 3 months
 
14. Legal incapacity or limited legal capacity
 
 |
| Study drug                                          | 
bisoprolol 5mg
 
atenolol 25mg/50mg
                                                                                                                                                                                                                                                                                                                                                                                                                                                                                                                                                                                                                                                                                                                                                                                                                                                                                                                                                                                                                                                                                                      |

|                                                         |                                    |
|---------------------------------------------------------|------------------------------------|
| Planned duration of observation for each subject | 1 month at least; 2 months at most |
|---------------------------------------------------------|------------------------------------|

### 3. Background

The sympathetic nervous system (SNS) plays a role in the pathophysiology of chronic arterial hypertension by modifying cardiac output and peripheral vascular resistance [1,2]. It is known that sympathetic nerve activity (SNA) can cause changes in blood pressure (BP) through the activation of baroreceptors [3,4]. Although introduced into scientific practice, methods of SNA evaluation are not commonly used in a clinical setting. Analysis of baroreflex sensitivity (BRS) and heart rate variability (HRV) have been recommended as the diagnostic tools for evaluating SNA and can be found in clinical guidelines as basic assessment methods [5-7]. Data suggest that low BRS and/or HRV are risk factors for cardiovascular morbidity and mortality [8-10].

Increasing clinical evidence suggests that central aortic pressure (CAP), but not brachial BP, predicts cardiovascular events, because the left ventricle (LV) pumps directly against the afterload in the central arteries. Moreover, aortic systolic BP, pulse pressure (PP), and augmentation index (AIx) have been shown to be strong independent cardiovascular risk predictors in hypertensive populations [11-15].

$\beta$ -blockers (BBs) are believed to improve SNS function; however, clinical studies on the effects of BBs on HRV and/or BRS in hypertensive patients have shown mixed results [16,17]. Moreover, it is noteworthy that in a series of studies [14,18-22], atenolol-based therapy was significantly less effective in lowering aortic systolic and pulse pressure than other hypertensive classes, which may be attributed to a different mechanism of atenolol, thus explaining the different clinical outcomes. Since  $\beta$ -blocking drugs might have heterogeneous effects on the arterial system and BRS depending on their pharmacologic properties, further comparisons of the effects of BBs on the arterial system and BRS may be helpful [23]. Bisoprolol with its high  $\beta_1$ -selectivity, long duration of action, and favorable

pharmacokinetic properties was shown to be an effective and safe antihypertensive agent [24,25]. Supposedly, these properties of bisoprolol should be an advantage in clinical practice.

Therefore, the present study was designed to compare the effects of a highly selective  $\beta_1$ -blocker (bisoprolol) and a classical  $\beta$ -blocker (atenolol) on SNA and CAP in hypertensive patients with controlled heart rate.

## **4. Study Objectives**

### **Primary objective**

To compare the efficacy in SNS activity and central blood pressure(CAP) of bisoprolol and atenolol in essential hypertensive patients with RHR>70bpm

### **Secondary objective**

1. To compare the effect in other SNS indication of bisoprolol and atenolol in EH patients with RHR>70bpm
2. To compare the efficiency of bisoprolol and atenolol to attaining RHR<65bpm]
3. To compare the efficiency of bisoprolol and atenolol on peripheral blood pressure

**To compare the safety and compliance of bisoprolol and atenolol treatment after RHR<65bpm**

### **4.1 Primary objective**

To compare the efficacy in SNS activity and central blood pressure(CAP) of bisoprolol and atenolol in essential hypertensive patients with RHR>70bpm

### **4.2 Secondary objective**

1. To compare the effect in other SNS indication of bisoprolol and atenolol in EH patients with RHR>70bpm
2. To compare the efficiency of bisoprolol and atenolol to attaining RHR<65bpm]
3. To compare the efficiency of bisoprolol and atenolol on peripheral blood pressure

## 5. Study Design

### 5.1 Study Design

It is a single-centers, randomized study in China, and planned to enroll 110 essential hypertension patients from 1 sites, who will be assigned to two groups randomly. All the inclusive patients will be consistent with the diagnosis of essential hypertension, and have a resting heart rate(RHR)  $\geq 70$  beats per minutes(bpm).

The inclusive patients will be assigned to two groups as follow (ratio 1:1)

Arm A: bisoprolol, 5-10mg/day for a targeting heart rate of less than 65 bpm(96)

Arm B: atenolol, 50-100mg/day for a targeting heart rate of less than 65 bpm (96)

The patient will receive bisoprolol 5mg Qd.(or atenolol 25mg Bid) for 2 weeks. If his/her heart rate<65bpm, this initial dose will be prolonged for another 2 weeks before the observation is over.

If the heart rate>65bpm, the patient will receive bisoprolol 7.5mg Qd.( or atenolol 37.5mg Bid) for 2 weeks. Then if his/her heart rate<65bpm, this increased dose will be prolonged for another 2 weeks before the observation is over.

If the heart rate>65bpm, the patient will receive bisoprolol 10mg Qd.( or atenolol 50mg Bid) for 2 weeks. Then if his/her heart rate<65bpm, this increased dose will be prolonged for another 2 weeks before the observation is over. If the heart rate>65bpm, the observation is over directly.

#### 5.1.1 Study flow

[figure not shown]

#### 5.1.3 Dosage adjustment

[figure not shown]

## 5.2 Trial design

### 5.2.1 Inclusion of Special Populations

This study will not include special populations such as children, pregnant women and subjects with genetic diseases.

## 5.3 Selection of Trial Population

### 5.3.1 Subjects enroll

All patients who meet the inclusion criteria but not the exclusion criteria can be enrolled into this study.

### 5.3.2 Inclusion Criteria :

- 25~65 years old
- Untreated mild to moderate EH
- Sinus rhythm
- RHR > 70bpm
- Can give written informed consent

### **5.3.3 Exclusion Criteria:**

- Atrial Fibrillation (AF)/ Sick Sinus Syndrome (SSS)/ atrioventricular block 2-3 grade(AVBII -III ) without pacemaker
- Bradycardia
- hypotensive
- Unstable Angina Pectoris (UAP)/AMI/ HF (NYHA class III - IV)
- Uncontrolled diabetes mellitus (DM)
- Bronchial asthma
- Gastro-intestinal ulcer or skin ulcer
- Liver dysfunction/ renal impairment
- Treated with CCB (Calcium antagonists) ( except amlodipine) or other beta blocker.
- Glaucoma
- Known allergic/ intolerance to beta blocker
- Pregnant or lactating women
- Participation in another clinical study within the last 3 months
- Legal incapacity or limited legal capacity

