## **7.1 Trial procedures and assessments**

### **7.1 Trial schedule and assessment contents**

The trial procedure and assessment contents are as follows:

1. Visit 1 -Week -1 (1 +3 day): this visit entails the following:

Before any procedures that are related to the trial is undertaken, informed consent of the patient should be obtained. Thereafter, basic information of the patient will be obtained and patients are screened for eligibility based on the inclusion and exclusion criteria.

- ①. Record birth date, gender, height, weight, waist circumstance, current medical condition and past medical history, including concomitant therapies.
- ②. Perform physical examinations, including vital signs (blood pressure, heart rate).
- ③. Blood tests: full blood count (white blood cells, neutrophils, red blood cells, hemoglobin and platelets), liver function (ALT, AST), renal function (Bun, Cr), fasting blood glucose and blood lipids (TC, TG, LDL-C and HDL-C).
- ④. 12-Lead ECG and echocardiography

- ⑤. Sepical tests: central blood pressure, BRS, BPV, HRV, Holter and 24 h-ABPM
2. Visit 2-Week 2 (14+3 days): this visit entails the following:
- ①. Perform physical examinations, including vital signs (blood pressure, heart rate), 12-Lead ECG.
  - ②. If the RHR is lower than 65 bpm, test BRS, BPV, HRV. Remain the treatment for an extended 2-week, then go for Last visit.
  - ③. Record AE and concomitant therapies.
3. Visit 3-Week 4 (28 +3 days): this visit entails the following:
- ①. Perform physical examinations, including vital signs (blood pressure, heart rate), 12-Lead ECG.
  - ②. If the RHR is lower than 65 bpm, test BRS, BPV, HRV. Remain the treatment for an extended 2-week, then go for Last visit.
  - ③. If the RHR is still higher than 65 bpm, adjust the dosage of bisoprolol or atenol according to blood pressure and heart rate. After 2 weeks, go for Visit 4.
  - ④. Record AE and concomitant therapies.
4. Visit 4-Week 6 (42+3 days): this visit entails the following:
- ①. Perform physical examinations, including vital signs (blood pressure, heart rate), 12-Lead ECG.
  - ②. If the RHR is lower than 65 bpm, test BRS, BPV, HRV. Remain the treatment for an extended 2-week, then go for Last visit.
  - ③. If the RHR is still higher than 65 bpm, directly go for Last visit.
  - ④. Record AE and concomitant therapies.
5. Last Visit- End of extended treatment:
- ①. Perform physical examinations, including vital signs (blood pressure, heart rate), 12-Lead ECG.

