#### **7.2.6 Special Tests**

11. Central blood pressure

Central blood pressure was performed by pressure tonometry using the integral software (SphygmoCor; AtCor Medical, Sydney, Australia) at the radial pulse, considering that this system has shown good repeatability of measurements. AIx, a measure of systemic arterial stiffness, was calculated as the difference between the second and first systolic peaks, expressed as a percentage of the pulse pressure. Because AIx depends on heart rate (HR), it was corrected for a HR of 75 bpm (AIxatHR75)

12. BRS, BPV and HRV

Measurements of SNA were performed after a 30-min rest in the sitting position. Patients were monitored noninvasively with a Finometer (Finapres Medical Systems, Amsterdam, The Netherlands; factory number: FMI. MU 00694, 00637; operation parameters: input: 220–240 V, 50–60 Hz, 100 VA) in both the supine (henceforth referred to as ‘lying’) and the standing positions. BRS was defined by the slope of the linear regression curve obtained by plotting the changes of SBP against the pulse interval. The mean value of the various slopes was calculated and used as the definitive BRS value for each subject [5,30-33]. HRV was calculated from the time-sequential analysis and was expressed as 3 components: low frequency (LF), high frequency (HF), and LF/HF ratio.

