## **8 Statistics**

### **8.1 Sample Size**

This study will recruit 110 patients with  $RHR \geq 70$  bpm and mild or moderate blood pressure.

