### **8.3 Endpoints**

#### **8.3.1 Primary Endpoint(s)**

The primary endpoint is BRS and central blood pressure at Last visit.

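### The rhythm exclusion spares pacemaker carriers, so a few patients whose pulse interval may be set by a device can enter a trial that measures baroreflex sensitivity and titrates on heart rate

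*Protocol*

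**What the plan says.** Section 5.3.3 of the protocol lists as its first exclusion "Atrial Fibrillation (AF)/ Sick Sinus Syndrome (SSS)/ atrioventricular block 2-3 grade(AVBII -III ) without pacemaker". The synopsis has the same condition, ending "atrioventricular block 2-3 grade(AVB II III) without pacemaker", so the qualifier is not a slip in one place. Neither says whether it applies to all three diagnoses or only to AV block. Section 5.3.1 gives the enrolment rule: "All patients who meet the inclusion criteria but not the exclusion criteria can be enrolled into this study". Section 5.3.2 requires sinus rhythm and a resting heart rate above 70 bpm, and section 5.3.3 separately excludes bradycardia. No criterion names a pacemaker as a reason for exclusion.

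On measurement, section 8.3.1 states: "The primary endpoint is BRS and central blood pressure at Last visit". Section 7.2.6 specifies that "BRS was defined by the slope of the linear regression curve obtained by plotting the changes of SBP against the pulse interval", and derives HRV as low-frequency power, high-frequency power and their ratio. Heart rate also steers the trial. Section 5.1 titrates each arm to a target, for example "bisoprolol, 5-10mg/day for a targeting heart rate of less than 65 bpm", and section 7.1 makes the interim tests conditional: "If the RHR is lower than 65 bpm, test BRS, BPV, HRV". Attaining a rate below 65 bpm is secondary objective 2. The protocol has no rule for paced beats in BRS, HRV or resting heart rate.

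**The concern.** A pacemaker carve-out is understandable where a rhythm exclusion serves only to protect patients from bradycardia. In this trial the behaviour of the heart rate is itself what is measured. BRS and HRV are informative only if the interval between beats is under autonomic control, and the titration rule presumes that the resting rate can respond to the drug.

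The entry criteria check the untreated rate. The difficulty arises later, when a rate-lowering drug may bring the sinus rate down to the point at which the device takes over. From then on, a primary endpoint and the variable that decides the dose path may reflect the device rather than the treatment.

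**Working it through.** The protocol states no figure to reproduce here. The check is a reading of the eligibility rules against the measurement rules, followed by two small calculations.

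**Step 1. Who can enter?** Inputs: the exclusion (5.3.3 and synopsis), the sinus rhythm and heart-rate criteria (5.3.2), the bradycardia exclusion (5.3.3) and the enrolment rule (5.3.1).

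| Pacemaker carrier with | Qualifier covers AV block only | Qualifier covers whole list |
|---|---|---|
| AF at screening | Barred (AF exclusion and sinus rhythm) | Barred (sinus rhythm) |
| Sick sinus syndrome, sinus rhythm above 70 bpm at screening | Barred | Eligible |
| AV block grade 2–3, atrial rhythm sinus above 70 bpm at screening | Eligible | Eligible |

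The last row holds on either reading, unless sinus rhythm is taken to exclude any paced rhythm, which the protocol does not say. A resting rate above 70 bpm would not ordinarily be called bradycardia, so that exclusion does not clearly close the gap.

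**Step 2. What happens to BRS and HRV while the device sets the interval?** A regression slope is Cov(SBP, interval) / Var(predictor). If the interval is constant, the covariance is 0. With the interval as response, the slope is 0 / Var(SBP) = 0; with the interval as predictor, it is 0/0 and undefined. A constant interval likewise has no low- or high-frequency power, and the LF/HF ratio is 0/0. This is the limiting case of continuous pacing at the lower rate during the recording. It does not describe a carrier whose own sinus node still drives the rate.

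**Step 3. What happens to the heart-rate target?** The programmed lower rate, L, is not in the documents, so both ranges are shown.

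- L of 65 bpm or above: while the device paces at L, resting rate cannot fall below 65. The patient goes through all three two-week steps of section 5.1 (2 + 2 + 2 = 6 weeks), then directly to the Last visit, without the two-week extension. The interim BRS and HRV tests, which require a rate below 65, are never triggered. (A rate of exactly 65 misses the target, but the protocol assigns it to neither branch.)
- L below 65 bpm: the patient entered above 70 bpm, so the sinus rate must still fall by more than 70 − 65 = 5 bpm to reach target. The device limits how far the rate can fall; it does not bring about the fall.

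**Step 4. Weight of one patient.** With 110 patients (8.1) allocated 1:1 (8.2), an arm has 110 / 2 = 55, and one patient is 1/55 = 1.8% of it. Section 5.1 also prints 96 beside each arm, which does not agree with 110; on that figure one patient is 1/96 = 1.0%. Either is a weight per patient and measures neither prevalence nor bias.

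**The case against.** The strongest reply is that the other criteria already do most of the work. Sinus rhythm removes patients in AF, and a rate above 70 bpm removes those resting at a lower backup rate. The qualifier may attach only to AV block. Who remains is a patient aged 25 to 65 with untreated mild to moderate hypertension, a pacemaker, and sinus rhythm above 70 bpm, at one site. The count could well be zero. Randomisation gives no reason to expect such patients to favour one arm. No device effect is shown on central blood pressure, the other primary endpoint. A pacemaker that follows the patient's own atrial rate may preserve part of the BRS signal.

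All of this stands as a limit on size. It does not close the gap, because the AV block carve-out admits carriers on either reading and the entry criteria look only at the rate before treatment.

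A reader might go further and infer that target attainment in these patients is fixed in advance by the programmed rate: always reached below 65, never reached at 65 or above. The documents do not support the first half. A patient who enters above 70 bpm reaches target only if the sinus rate slows. The second half depends on a setting that the protocol does not give. Nor do the documents support saying that every endpoint in a pacemaker carrier reflects device programming; that holds for BRS and HRV only while the device sets the interval.

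**Conclusion.** The exclusion as worded lets in pacemaker carriers with second- or third-degree AV block, and possibly with sick sinus syndrome, if they are in sinus rhythm above 70 bpm at screening. In such a patient, BRS and HRV at the Last visit may not measure autonomic control, and resting heart rate has a floor. At a lower rate of 65 bpm or above, progression through the titration steps would be unrelated to drug response.

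This rests on two assumptions: that treatment slows the sinus rate to the device's lower rate, and, for the titration effect, that this rate is 65 bpm or above. The number of patients is probably very small and cannot be estimated from the protocol. What is at stake is uninformative values in a primary endpoint, at 1.8% of an arm per patient, with no direction of bias shown. The point is modest, but the correction is simple enough that it should be made.

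**What to change.** Reconcile the synopsis with sections 5.3.2 and 5.3.3. Delete the words *without pacemaker* in both exclusion lists, so that AF, sick sinus syndrome and AV block grade 2–3 are excluded outright, and add an implanted pacemaker as a separate exclusion, stated to be on measurement grounds (BRS, HRV and resting heart rate). Deleting the qualifier also settles its scope.

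Visit 1 in section 7.1 already includes medical history, a 12-lead ECG and Holter monitoring, so no new procedure is needed. The cost is a short amendment to two lists and the loss of a few candidates.
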